#### Smartphones

An iPhone SE smartphone will be provided to participants without access to a personal smartphone. Devices will be provided to participants with a scheduled return date. Once returned, iPhones will be sanitized and recharged, and all device histories (calls, browser, and SMS text message) will be cleared. If participants do not return the study-provided iPhone and become unreachable, they will be considered dropped from the study.

#### Data Collection and Management

The study app is Health Insurance Portability and Accountability Act (HIPAA) compliant and will transmit daily diary and GPS data to a Crowdbotics-hosted administrator panel, also HIPAA compliant, eschewing sensitive, identifiable data storage on participants’ personal devices. GPS data collection will occur continuously, recording latitudinal and longitudinal points at 1-minute intervals. In both arms, participants will be prompted twice each day by SMS text message to complete their daily diary items within a 3-hour window (9 AM-noon and 6 PM-9 PM) whenever ready and able to find privacy.

The aim-3 daily diary items are shown in Multimedia Appendix 3.

Throughout the conduct of the aim-3 trial, data will be securely stored on REDCap, and data sets that are downloaded for analysis will be stored on secure Tulane-hosted Box cloud servers. NOLA GEM user-level paradata, including daily diary responses, will be downloaded from the HIPAA-compliant Crowdbotics-hosted administrator panel, manually cleaned, and transformed into a standard “wide” data format in which each row corresponds to a unique participant using dedicated R scripts (R Foundation for Statistical Computing).

#### Data Safety Monitoring

All data collected will be monitored weekly by the research staff to ensure the privacy and confidentiality of the participants. General quality assurance checks will also be run on the data during and after collection. Any adverse events or unanticipated problems will be reported immediately to the institutional review board. To ensure the confidentiality of the data, each participant is assigned a unique identifier that will not be linked to any identifying information. Any technology used (Zoom, Qualtrics, NOLA GEM app, or REDCap) is HIPAA secure. All SMS text message–delivered reminders sent to participants during the research period will be generic and will have no specific content in case participants wish to keep their participation private.

#### Intervention Arm

Intervention arm participants will be provided access to the SMS text message prompts; daily diary interface; a resource list that covers local health care, housing, domestic violence, family, and mental health services; a “My Progress” screen where they can track elements of their interaction with the app; and the full suite of LIFT sessions, skills, and SkillChecks. Following the submission of each daily diary, the study app will recommend specific LIFT content based on participants’ particular patterns of momentary stressors. In addition, participants can access all content in their own time.

#### Control Arm (GEMA Alone)

Control arm participants will have access to the SMS text message and daily diary functions exclusively plus the resource list provided to treatment arm participants.

### Primary Outcomes

Primary, distal outcome measures will be assessed at the immediate postintervention time point (within 1 week of completing the 21-day intervention period) and the 30- and 90-day follow-up assessments, as specified in the following sections.

#### Acceptability, Feasibility, and Usability

JITAI-specific proximal outcomes have been summarized previously. The aim-3 distal outcomes and their precise operationalization are outlined in this section.

Feasibility and acceptability will be assessed after participation in the 21-day trial period. Feasibility will be operationalized via screening and enrollment rates; completion rates of daily diaries; and paradata describing within-person patterns of use, including JITAI-triggered prompts [61,117]. Acceptability will be operationalized as follows. Intervention arm participants will complete the *User Experience Questionnaire* (short version), with ratings of the NOLA GEM app’s pragmatic and hedonic quality User Experience Questionnaire domains assessed against available benchmarks [118]. The single-item *Net Promoter Score* will ask about participants’ likelihood to recommend NOLA GEM on a 0 to 10 scale [119]. Both measures will be administered at the immediate postintervention assessment.

Attrition rates will also be recorded, and those who drop out of the study will receive a set of questions exploring motivations for discontinuation wherever possible.

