**Methods:**

The development of NOLA GEM entailed identifying real-time tailoring variables via a geographic ecological momentary assessment (GEMA) study (n=49; aim 1) and place-based and user-centered tailoring, responsive to the unique cultural contexts of HIV survivorship in New Orleans, via formative interviews (n=12; aim 2). The iOS- and Android-enabled NOLA GEM app leverages twice-daily GEMA prompts to offer just-in-time, in-app recommendations for effective coping skills practice and app-delivered *Living in the Face of Trauma* session content. For aim 3, the pilot trial will enroll an analytic sample of 60 New Orleans people living with HIV individually randomized to parallel NOLA GEM (intervention) or GEMA-alone (control) arms at a 1:1 allocation for a 21-day period. Acceptability and feasibility will be assessed via enrollment, attrition, active daily use through paradata metrics, and prevalidated usability measures. At the postassessment time point, primary end points will be assessed via a range of well-validated, domain-specific scales. Care engagement and viral suppression will be assessed via past missed appointments and self-reported viral load at 30 and 90 days, respectively, and through well-demonstrated adherence self-efficacy measures.

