#### Sample Size Considerations

The target sample size is approximately 100, which will accommodate an anticipated ≥10% attrition rate based on previous experience enrolling local violence-affected in-care people living with HIV, for an optimal analytic sample of 60 (30 per arm).

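### The two acceptability ratings are planned only at the postintervention assessment and are not extended to dropouts, so they are likely to be optimistic if people who dislike the app leave

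*Protocol article*

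**What the plan says.** Under Acceptability, Feasibility, and Usability, the protocol article defines acceptability by two ratings. Intervention-arm participants complete the short User Experience Questionnaire, whose domains are compared with available benchmarks. The single Net Promoter item "will ask about participants’ likelihood to recommend NOLA GEM on a 0 to 10 scale". The timing is explicit: "Both measures will be administered at the immediate postintervention assessment". The Primary Outcomes section places that assessment "within 1 week of completing the 21-day intervention period".

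Dropouts are covered by a separate sentence: "those who drop out of the study will receive a set of questions exploring motivations for discontinuation wherever possible". Neither rating is mentioned there, and no other section extends the ratings to people who leave.

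The same section records attrition. The abstract's Methods paragraph takes a wider view of the construct: "Acceptability and feasibility will be assessed via enrollment, attrition, active daily use through paradata metrics, and prevalidated usability measures". The ratings stand under the heading Primary Outcomes, although aim 3 in Study Objectives applies the word primary to the continuum-of-care end points.

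**The concern.** Disliking an app is a plausible reason to leave a study of that app. If the ratings are sought only from those who reach the final assessment, the least satisfied users may be under-represented. The Net Promoter Score, and the User Experience Questionnaire result set against its benchmarks, would then be too favourable for the group that was given the app.

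This is a question of data collection. A rating that was never requested cannot be recovered later by an analysis plan. Acceptability is one of the properties that aim 3 sets out to test, and the Results section says the pilot is meant to support an application for a full-scale trial. The Limitations section does not mention the selection.

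**Working it through.** **Loss to be expected.** The plan gives no acceptability figure to reproduce. The only figures on loss are in Sample Size Considerations: about 100 enrolled, at least 10% attrition, 60 analysed.

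- Enrolment needed for 60 at 10% loss: 60 / (1 - 0.10) = 66.7, so 67, not about 100.
- Retained from 100 at 10% loss: 100 x 0.90 = 90, not 60.
- Loss implied by going from 100 to 60: 1 - 60/100 = 40%.

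The three figures do not reproduce one another. That is a separate matter, but it means the plan does not settle the likely loss. The stated minimum of 10% is used here. With about 100 participants allocated 1:1, it corresponds to about 0.10 x 50 = 5 intervention-arm participants.

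**Effect on the Net Promoter Score.** The score is the percentage of promoters minus the percentage of detractors, so it averages over groups. With d the unrated share, S_c the score of those rated and S_d the score that dropouts would have given:

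- Score over all users: S_all = (1 - d) x S_c + d x S_d
- Excess of the reported score: S_c - S_all = d x (S_c - S_d)

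S_c = +30 and all values of S_d are assumptions, because the plan gives neither. With d = 0.10:

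| Dropouts' score | Score over all users | Excess |
|---|---|---|
| +30 (no difference) | 27 + 3 = +30 | 0 |
| 0 | 27 + 0 = +27 | 3 |
| -30 | 27 - 3 = +24 | 6 |
| -50 | 27 - 5 = +22 | 8 |
| -100 (all detractors) | 27 - 10 = +17 | 13 |

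The excess is proportional to d. Doubling the loss to 20% (illustrative) gives 24 - 6 = +18 for dropouts at -30, and 24 - 20 = +4 if all are detractors.

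**Effect on the mean of the 0 to 10 item.** The excess is d times the gap between those rated and dropouts. At d = 0.10, a gap of 1 point gives 0.1 and a gap of 3 points gives 0.3. If dropouts rated the app 1 point higher, the sign reverses: -0.1.

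**User Experience Questionnaire.** The article gives neither a benchmark value nor an expected score, so no corresponding figure can be computed.

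**The case against.** The strongest reply is that dropout is already visible. Attrition, active use and diary completion are collected, reasons for leaving are sought, and the Discussion plans open-ended usability interviews around offboarding. A good rating beside high attrition would not mislead a careful reader. Rating an app after the full 21 days is also a defensible choice, and a condensed article need not list every item in the dropout question set. Much of this stands, and it makes the point smaller. It does not remove it: attrition and reasons for leaving give no rating on either scale, and the text assigns both ratings to one time point.

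Four stronger readings are tempting, and the documents do not support them.

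- **That the ratings are biased upward as a fact.** This needs a gap between dropouts and those rated, and the documents give none. If there is no gap, there is no bias.
- **That anyone who stops using the app goes unrated.** The assessment follows the 21-day period and carries no usage threshold. Study Settings allows later steps by phone, so a non-user who stays in the study can still be rated. Only people who miss the assessment are affected.
- **That 40% of users will be unrated.** With all dropouts detractors, that would give 0.60 x 30 - 0.40 x 100 = -22. But 40% is not a planned rate; it comes from the unreconciled sample-size figures. Under Participants and Procedures, randomization precedes the visit at which consent is obtained and the app installed, so part of that loss could be people who never used the app.
- **That these scores decide whether a full trial follows.** No threshold is set on either. The abstract's Conclusions rest the future trial on sustained adoption and early efficacy.

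Contact with dropouts is also not assured. Under Smartphones, some are classed as dropped partly because they cannot be reached.

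**Conclusion.** The point holds as an inexpensive improvement. As written, both ratings describe participants who reach the postintervention assessment, and optimism is the likely direction if dissatisfied users leave. At the stated minimum attrition and an assumed score of +30 among those rated, the Net Promoter Score would be too high by 0 to 13 points across the cases shown, from equal ratings to all dropouts being detractors. The gap grows in proportion to attrition, which the plan does not pin down. Its size, and even its sign, rest on the unknown ratings of people who leave. No effect on the benchmark comparison has been shown.

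**What to change.** Add the Net Promoter item and the short User Experience Questionnaire to the dropout contact for intervention-arm participants who were onboarded to the app. Then:

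- report both ratings with the number of onboarded intervention users as the denominator, and the response rate and attrition beside them;
- show ratings given at discontinuation separately, since they follow partial exposure;
- for the Net Promoter Score, add a sensitivity result that counts non-respondents first as non-promoters who are not detractors, then as detractors. In the example above at 10% non-response, these give +27 and +17.

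If the full protocol's dropout question set already contains the two measures, only the description and the reporting need to change.

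The cost is a few extra items in a contact that is already planned, with no new visit. Response will be incomplete because some dropouts are unreachable, and the score may be less favourable. The article reports recruitment from July 2023, so added items would reach only later dropouts. The reporting changes can cover everyone.

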#### CoC Milestones

Primary outcomes, representing recognized HIV CoC milestones [1,21,23], will be operationalized as follows via a postassessment survey.

##### Care Engagement

Past-30-day outpatient retention will be assessed using the 12-item *HIV Treatment Adherence Self-Efficacy Scale*. A well-validated measure, the HIV Treatment Adherence Self-Efficacy Scale recognizes care engagement as a holistic, psychosocially, and environmentally contingent construct, with particular attention to personal routine [120]. In addition, participants will self-report the percentage of appointments they missed in the past 90 days at their 90-day follow-up assessment.

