### Study Objectives

This study aims to develop, pilot, and refine *NOLA GEM*, a smartphone-delivered LIFT adaptation informed by within-person geographic ecological momentary assessment (GEMA) data on time-variant stressors and symptom profiles among violence-affected people living with HIV in New Orleans [49]. Mobile health (mHealth) and internet-delivered interventions that activate evidence-based, trauma-informed psychotherapies have shown promise in enacting clinically significant PTSD improvement [50,51], with a 2018 Cochrane review pointing toward opportunities to bolster the evidence base and calling for closer attention to mechanisms of change [52]. The benefits of mHealth in advancing CoC milestones are well established [53,54], although innovations in cultural and contextual tailoring are urgently needed to ensure sustainability [55-57]. These benefits can be augmented by in-app geospatial awareness, building on prior work that leverages GPS to (for example) alert mHealth users to the proximity of HIV and sexual and reproductive health clinics [58,59] or, in contrast, use real-time GPS coordinates to (1) describe routine activity paths and (2) apply this geospatial awareness at a hyperlocal level to address the potential of spatial-environmental stressors to evoke traumatic stress and drive CoC churn and, alternatively, identify restorative spaces to reduce stress. By developing NOLA GEM, we engage these opportunities to advance the field; meet the needs of New Orleans people living with HIV [41,45,46]; and address the nonlinear, holistic nature of traumatic stress [1,2,4,8] by delivering effective coping skills education and reinforcement in real time [33].

We will engage these objectives via the following specific aims:

*Aim 1*: conduct GEMA with violence-affected people living with HIV to (1) describe activity spaces associated with CoC and (2) assess potential mediated pathways through mood, mental health, substance use, trauma cognitions, and coping to inform novel intervention targets.*Aim 2*: develop NOLA GEM, an mHealth LIFT adaptation, incorporating GEMA-informed mediators of well-being tailored for New Orleans people living with HIV.*Aim 3*: test the feasibility, acceptability, and preliminary efficacy of the NOLA GEM app against GEMA alone on primary CoC (care engagement, ART adherence, and viral suppression) and secondary mental well-being end points.

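### Care engagement, a primary outcome, labels an adherence self-efficacy scale as outpatient retention, and the abstract and body disagree on when missed appointments are measured

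*Protocol article*

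**What the plan says.** Study Objectives (aim 3) names "primary CoC (care engagement, ART adherence, and viral suppression) and secondary mental well-being end points". The CoC Milestones section repeats the status: "Primary outcomes, representing recognized HIV CoC milestones". Care engagement is therefore primary.

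The Care Engagement section gives it two measures:

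- A scale: "Past-30-day outpatient retention will be assessed using the 12-item" "HIV Treatment Adherence Self-Efficacy Scale". The reason given is that the scale "recognizes care engagement as a holistic, psychosocially, and environmentally contingent construct, with particular attention to personal routine".
- A visit-based item: "participants will self-report the percentage of appointments they missed in the past 90 days at their 90-day follow-up assessment".

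The abstract (Methods) describes the same outcome differently: "Care engagement and viral suppression will be assessed via past missed appointments and self-reported viral load at 30 and 90 days, respectively". The sentence then adds adherence self-efficacy measures as a further item.

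The ART Adherence section covers adherence as its own primary domain, with a visual analog scale for the share of medication taken in the past 30 days.

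**The concern.** Retention in outpatient care is a behaviour: visits were kept or they were not. A self-efficacy scale records how confident someone feels. Putting the first label on the second measure means that a result table headed retention would hold no retention data.

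The direction of the possible error matters. NOLA GEM teaches coping skills, and the Background section describes one of the LIFT techniques as countering thoughts that erode self-efficacy. A confidence score is the sort of measure such an app might move first, whether or not attendance follows. The Results section says that the pilot will be used to prune app components that look ineffective and to support an application for a full-scale trial, so a mislabelled primary outcome would feed both decisions.

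The time point is a separate fault. If the abstract and the body disagree on when a primary outcome is measured, a reader cannot tell which analysis was planned.

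**Working it through.** The plan states no figure on this point, so there is none to reproduce. The check sets the texts side by side.

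**1. What does the scale measure?**
- Label in Care Engagement: outpatient retention over the past 30 days.
- Instrument: a 12-item scale whose title says treatment adherence self-efficacy.
- Abstract, same outcome: "past missed appointments and self-reported viral load at 30 and 90 days, respectively, and through well-demonstrated adherence self-efficacy measures". Self-efficacy is listed beside missed appointments as a different thing, and is called adherence self-efficacy.

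The title and the abstract agree with each other and disagree with the label.

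**2. Is it distinct from the other primary domains?** ART adherence is already a primary domain with its own measure. A score for confidence in adherence sits nearer to that domain than to clinic attendance, so it does not separate care engagement from adherence.

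**3. Where does the protocol place self-efficacy elsewhere?**
- Aim 1 Overview: domain-general self-efficacy is among the possible mediating pathways, to serve as an intervention target or proximal outcome.
- Effective Coping: the Coping Self-Efficacy Scale is a secondary outcome.
- Care Engagement: adherence self-efficacy is part of a primary, distal outcome.

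These are related but not identical constructs, so closeness to the mechanism is a reasoned inference and not something the documents demonstrate.

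**4. When are missed appointments measured?**

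| Source | Missed appointments | Viral load |
|---|---|---|
| Abstract, pairing the items in order | 30 days | 90 days |
| Care Engagement and Viral Suppression sections | 90 days | 90 days |

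If the abstract is instead read as giving both time points for both items, it still differs from the body, which gives only 90 days for each.

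**5. What can the percentage item bear?** Percentage missed = 100 × missed / scheduled.
- Scheduled = 0: 0/0, undefined.
- Scheduled = 1: only 0% or 100% is possible.

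How many participants would have no visit in 90 days depends on visit spacing, which the documents do not give. With an assumed interval of *d* days, the share with none is max(0, 1 − 90/*d*) for evenly spaced visits and exp(−90/*d*) for random (Poisson) visits, at 30.4375 days per month:

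| Assumed interval | Evenly spaced | Poisson |
|---|---|---|
| 2 months | 0% | 23% |
| 3 months | 1% | 37% |
| 4 months | 26% | 48% |
| 6 months | 51% | 61% |
| 12 months | 75% | 78% |

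Of the 60 to be analysed, that is 0 to about 47 (0.782 × 60 = 46.9). A range this wide shows only that the documents cannot size the issue.

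**The case against.** The strongest defence is that nothing is hidden. The article names the scale, gives a reason for it, and in the abstract calls it a self-efficacy measure next to missed appointments. The items are not shown, so the scale is being judged by its title. The Limitations section also says that the pilot is underpowered by design for formal efficacy testing, and it is speculation that anyone would in fact announce better retention.

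Part of this stands. Readers of the abstract are told what kind of measure it is, and a misleading report is a risk, not a certainty. But viewing engagement as a broad psychosocial construct does not turn a confidence score into a record of visits, and the body attaches the word retention to it. Pilot status does not help either, since the pilot's results are meant to guide the next trial.

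A reader might go further and infer that the missed-appointment item rewards leaving care, because someone who books nothing could answer 0% missed. The documents do not support stating this as fact. The article gives neither the item wording nor the scoring, and a not-applicable option, a visit count or a rule for no appointments could stand in the questionnaire or analysis plan, which are not shown. The parent-study criteria, which aim 3 carries over, also require being in care at an HIV clinic, although community recruitment leaves some room.

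**Conclusion.** The point holds in two parts, both resting on the article's own wording. First, a primary outcome applies the name of a behaviour to a scale that, by its title and by the abstract, measures confidence in treatment adherence. Second, the time point for missed appointments conflicts between the abstract (30 days) and the Care Engagement section (90 days).

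The undefined percentage when no visit was scheduled is true by arithmetic, but it is only a reason for a safeguard. The article's silence on scoring does not show that such participants would be counted as perfectly engaged, and no defensible number per arm can be put on them.

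The conclusion assumes that the scale's content matches its title. It does not depend on visit frequency. This should be corrected because it affects what a primary result may be called, but it does not threaten the trial's conduct.

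**What to change.** 1. Make self-reported attendance the care-engagement outcome.
2. Report the HIV Treatment Adherence Self-Efficacy Scale under its own name, as a secondary psychosocial outcome.
3. State one time point and look-back window for missed appointments and use it in both the abstract and the Care Engagement section.
4. As a safeguard, ask for the number of HIV visits scheduled and the number missed, with a 'none due' option. Analyse missed/scheduled among participants with at least one scheduled visit. Report those with none separately by arm, split into none due and out of care, and code them neither as perfect nor as failures. A composite that counts having no visit scheduled as a failure should be avoided, because it would misclassify stable patients who were not due.

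Cost: items 1 to 3 need only changes of wording and outcome status, with no new data. Item 4 replaces one question with two plus a response option. Its drawback is that having a scheduled visit arises after randomisation, so the comparison among those with one is not fully protected by randomisation. That is why the count without one should be shown for each arm. Because recruitment has begun, the change should be dated and recorded before outcome data are compared by arm; participants already past the 90-day assessment will have only the percentage item.
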